## Abstract

**Background:**

Improving the rates of, and instruments used in, screening for perinatal depression and anxiety among Aboriginal and Torres Strait Islander women are important public health priorities. The Kimberley Mum’s Mood Scale (KMMS) was developed and later validated as an effective and acceptable perinatal depression and anxiety screening tool for the Kimberley region under research conditions. Other regions have expressed interest in using the KMMS with perinatal Aboriginal and Torres Strait Islander women. It is, however, important to re-evaluate the KMMS in a larger Kimberley sample via a real world implementation study, and to test for applicability in other remote and regional environments before recommendations for wider use can be made. This paper outlines the protocol for evaluating the process of implementation and establishing the ‘real world’ validity and acceptability of the KMMS in the Kimberley, Pilbara and Far North Queensland in northern Australia.

**Methods:**

The study will use a range of quantitative and qualitative methods across all sites. KMMS validation/revalidation internal consistency of Part 1 will be determined using Cronbach’s alpha. Equivalence for identifying risk of depression and anxiety compared to a standard reference assessment will be determined from receiver operating characteristic curves. Sensitivity and specificity will be determined based on these cut-points. Qualitative methods of phenomenology will be used to explore concepts of KMMS user acceptability (women and health professionals). Additional process evaluation methods will collate, assess and report on KMMS quality review data, consultations with health service administrators and management, field notes, and other documentation from the research team. This information will be reported on using the Dynamic Sustainability Framework.

**Discussion:**

This project is contributing to the important public health priority of screening Aboriginal and Torres Strait Islander women for perinatal depression and anxiety with tools that are meaningful and responsive to cultural and clinical needs. Identifying and addressing barriers to implementation contributes to our understanding of the complexity of improving routine clinical practie.

**Trial registration:**

The study was registered retrospectively on 15/05/2019 with the Australian and New Zealand Clinical Trial registry (ACTRN12619000580178).

## Background

There is little evidence of the prevalence of perinatal depression and anxiety among Aboriginal and Torres Strait Islander women in Australia [1–3]. Given the higher levels of trauma and distress in the Aboriginal population as a whole, it is understood that rates of perinatal depression and anxiety are also higher than the national average [1–4]. Untreated perinatal mental health disorders can have a severe negative impact on the mother, child and extended family [1, 4, 5]. Specific impacts of perinatal depression and anxiety may include poorer birth outcomes, poorer bonding and attachment between mother and baby, ongoing emotional and cognitive difficulties for children, and enduring (and possibly escalating) mental health disorders for the woman [6–8].

In 2008, the Australian Government launched the National Perinatal Depression Initiative 2008–2013 [9], promoting a universal clinical screening schedule for perinatal depression. The Edinburgh Postnatal Depression Scale (EPDS) [10] was the recommended clinical screening tool. The EPDS was developed in 1987 and is a 10-item depression scale, which also includes a 3-item anxiety subscale. The EPDS, however, has not been validated for use with Aboriginal and Torres Strait Islander women [11]. In the Kimberley, a sparsely populated region in North West Australia, health professionals were concerned that the language and concepts in the EPDS unintentionally disengaged Aboriginal women from the screening process [12]. Consequently, use of the EPDS has been limited among Aboriginal women, and perinatal depression and anxiety are often not identified [12, 13]. In 2013 Gausia et al. [3] reported that Aboriginal women were four times less likely to be screened than non-Indigenous women. Another recent study from Queensland (*n* = 30,468) demonstrated that, after adjustment for socio-demographics, Aboriginal and Torres Strait Islander women were approximately half as likely to have been screened using the EPDS than non-Indigenous women (OR 0.47, 95% CI 0.39–0.56) [14]. Improving the rates of, and instruments used in, screening for perinatal depression and anxiety among Aboriginal and Torres Strait Islander women are important public health priorities.

To initiate improvements in perinatal depression and anxiety screening in the Kimberley region, over 100 Aboriginal women and 70 staff from Kimberley Aboriginal Community Controlled Health Organisations (ACCHOs) and the Western Australian Country Health Service (WACHS) were consulted. The objective of the consultation was to develop a more appropriate way for health professionals to engage Aboriginal women and screen for perinatal depression and anxiety [12]. The consultation resulted in the development of the two-part Kimberley Mum’s Mood Scale (KMMS) (Additional file 1). Part 1 of the KMMS adapts the EPDS using language and graphics determined through the consultation process. Part 2 involves “yarning” [15, 16] as a culturally secure approach for health professionals to explore select psychosocial risk and protective factors with women. The yarning topics were identified through both the consultation process and existing resources [17] relating to good psychosocial care in the perinatal period for Aboriginal and Torres Strait Islander women. The KMMS is designed to be administered by providers of perinatal care including midwives, child health nurses (CHNs), Aboriginal Health Workers (AHWs) and remote area nurses (RANs) who complete the tool alongside and in partnership with Aboriginal and Torres Strait Islander women.

In 2013–14, the KMMS was validated in a study with 91 Aboriginal women from 15 communities and towns in the Kimberley [13]. Overall KMMS risk equivalence for screening for clinically diagnosed depression and anxiety disorders was greater than or equal to moderate (sensitivity 83%; specificity 87%; positive predictive value 68%). During the validation study, participants and their health professionals were asked, using short semi-structured surveys, about their experience with, and the acceptability of, the KMMS. Results from the survey demonstrated the KMMS was well-accepted by the participants and their health professionals. The Aboriginal women who participated in the Kimberley validation study placed high value on patient–health professional rapport and having the time and opportunity to yarn. Completing the tool with a health professional rather than alone was also highly valued.

The findings of the Kimberley validation study [13] have led to endorsement of the KMMS by the Kimberley Aboriginal Health Planning Forum (KAHPF) as the recommended perinatal depression and anxiety screening tool for all Aboriginal and Torres Strait Islander women in the Kimberley region [18]. To better embed the KMMS into routine clinical practice we need to understand ‘real world’ KMMS utilisation/implementation, such as quality, clinical support required and acceptability. We also need to test the validity of the KMMS at a population level, i.e., ‘revalidate’ the KMMS in a larger Kimberley sample via a real world implementation study. Other regions in Australia have also expressed interest in using the KMMS with Aboriginal and Torres Strait Islander women during the perinatal period. Before recommendations for wider use can be made, we need to test for applicability in other regions. This paper outlines the protocol for evaluating the process of implementation and establishing the ‘real world’ quality, validity and acceptability of the KMMS in the Kimberley, Pilbara and Far North Queensland (FNQ) regions of Australia.

## Methods/design

### Objectives

The primary objectives of this study are to 1) evaluate the implementation and real-world performance of the KMMS in the Kimberley; 2) test the validity of the KMMS in the Pilbara and FNQ; and 3) assess the acceptability of the KMMS for Aboriginal and Torres Strait Islander women and their health professionals across all sites, i.e. Kimberley, Pilbara and FNQ.

### Partnerships

The study is a partnership with Apunipima Cape York Health Council (ACYHC) in FNQ; WACHS – Pilbara and Mawarnkarra Health Service (MHS) in the Pilbara region of Western Australia; WACHS – Kimberley, and Kimberley Aboriginal Medical Services (KAMS) and its member services across the Kimberley region of Western Australia.

### Study populations

The target populations for this study are Aboriginal and Torres Strait Islander women who are accessing perinatal care in selected sites in the Kimberley, Pilbara and FNQ, and their health professionals.

Sample frame A: Aboriginal and Torres Strait Islander women (aged 16 years and over) who are at least 6 weeks pregnant or between 7 days and 12 months post-partum, who are not known to be currently acutely mentally unwell and who can provide informed consent.

Sample frame B: Health professionals providing care to perinatal Aboriginal and/or Torres Strait Islander women (as per the specifications of sample frame A), including but not limited to midwives, CHNs, AHWs and RANs.

#### Recruitment

All women who meet the inclusion criteria (sample frame A) and are receiving perinatal care from a partner health service will be invited to participate in the study when they receive routine perinatal screening by perinatal health professionals. Women will be provided with an information sheet and will be required to provide written informed consent prior to participating in the study.

Women are able to withdraw consent at any time and their data will be withdrawn from the study results if they request this.

## Study process

The study involves assessment of implementation, validation/revalidation and acceptability of the KMMS as outlined in Fig. 1.

**Fig. 1 Fig1:**
[figure not shown]
Overview of KMMS and Study Process

### The KMMS

Part 1 of the KMMS (modified version of the EPDS) includes 10 close-ended questions using regionally appropriate language and graphics. It is an important way to introduce concepts and language around perinatal depression and anxiety, with which women may be unfamiliar [2, 12].

Part 2 is a psychosocial yarning tool [15, 16]. The domains covered in Part 2 include: support; stressors; self-esteem; childhood experiences; relationships; substance use; and social, emotional and cultural wellbeing. Part 2 aims to identify protective and risk factors that may positively or negatively influence a woman’s sense of wellbeing and risk of perinatal depression or anxiety. Health professionals are provided with open-ended prompts to help facilitate the yarn (Additional file 2) [19].

After the KMMS is completed, health professionals then use their clinical judgement and experience to interpret Part 1 and Part 2 to determine a woman’s overall risk of perinatal depression and anxiety. Categories are: low risk (self-care recommended); moderate risk (clinical assessment within 1 week); and high risk (clinical assessment within 72 h). Any concerns regarding a woman’s risk of harm to herself or others (as raised in Part 1, question 10; Additional file 3) requires immediate action in accordance with the health service policies/protocols.

In the Kimberley it is recommended regional practice for all Aboriginal women to be screened with the KMMS (18) with the same frequency and timing as the national EPDS screening schedule [4]. When repeating screening on the same woman during the same perinatal period, a new Part 1 is completed; however, the yarn in the original Part 2 is continued as opposed to starting Part 2 from the beginning. It is recommended practice for those scoring moderate or high risk on the KMMS at any stage to have further clinical assessment by a general practitioner (GP) or mental health professional [18].

#### Training perinatal health professionals

All perinatal health professionals in partner health services will be offered approximately 2–3 h of KMMS training. Training will be divided into three sessions:
KMMS in-service (50 min) designed to be delivered to all clinical staff. This training will provide information and awareness on perinatal mental health and wellness, provide an overview of the KMMS and ensure that all clinical staff are aware of the KMMS project.KMMS administrator training (1.5–2 h) designed to be delivered to health professionals who will be administering the KMMS. This will provide an in-depth explanation of how to use the KMMS, determining the overall risk level and how to recruit and consent women to the study.KMMS Diagnosis and Management Tool training (50 min). GPs and mental health professionals will be provided with specialist training in how to use the standard reference assessment, called the KMMS diagnosis and management tool (DMT; Additional file 4). This training will provide an overview of the KMMS screening process, the origins of the DMT and how to use the DMT as part of diagnosis and management of perinatal depression and/or anxiety.

All training will be provided face-to-face or via online classroom workshops. For health professionals involved in the KMMS administrator or DMT training, support and mentoring in using the KMMS tools will be available for the duration of the study.

#### Administering the KMMS

Perinatal health professionals from partner health services trained in the KMMS will consent participants and administer the KMMS instead of the EPDS in accordance with the KMMS guidelines for administration [19]. All women who are assessed as having an overall KMMS risk of moderate or high will be referred for further assessment; where possible this assessment will use the DMT. As part of this study, a proportion of women with an overall KMMS risk assessment of ‘low’ will also be referred for further assessment using the DMT to confirm that the current cut-point between low and moderate is valid.

#### Further clinical assessment

The DMT is the standard reference assessment for all further KMMS clinical assessments. Diagnosis is based on the Diagnostic and Statistical Manual of Mental Disorders (DSM IV) criteria for depressive and anxiety disorders [20] and severity (i.e. low, moderate, high) on the GP Mental State Examination [21]. Participants who are referred for an assessment using the DMT will be assessed as soon as practicable after the KMMS is administered. For those diagnosed with perinatal depression and/or anxiety, a follow-up management plan will be negotiated between the participant and the GP / mental health professional, ensuring appropriate support, referrals and treatment is discussed and agreed upon by both the woman and the health care professional.

### Proposed intervention

The proposed intervention (KMMS) for the three geographical areas is outlined below.

#### Kimberley implementation study

It is recognised that health service implementation is a complex undertaking with many promising research findings failing to translate into improved patient outcomes [22, 23]. Using the Dynamic Sustainability Framework (DSF) [24] we seek to explore and report on the process of implementation. This includes an examination of how the intervention (components, practitioners, outcomes, delivery platform), practice setting (staffing, organisational culture, information systems, business model, training and supervision), and ecological settings (population characteristics, policy, regulation, funding) enable or inhibit implementation of the KMMS into routine clinical care. Specific to the DSF is the expectation that “change is a constant and thus the success of an intervention to be sustained over time lies in the measured, negotiated, and reciprocal fit of an intervention within a practice setting and the practice setting within the larger ecological system” [24]. The DSF posits that ‘fit’ involves the way an intervention is delivered, the characteristics of patients, providers and settings, and the broader system within which health care is situated [24]. The DSF’s recognition and embrace of the constancy of change is compelling and speaks to the realities of the Northern Australian health workforce which is characterised by high turnover, low stability and high use of temporary staffing [25]. Similarly, the emphasis the DSF places on ‘fit’ seems a pertinent starting point for evaluating the process of implementing the KMMS across the geographically large and culturally diverse region of the Kimberley. The learnings and reflections from the process of implementation will be shared with partner health services and the KAHPF, and submitted to relevant peer reviewed journals and national interest bodies contributing to the science of ‘what works’ in the validation and implementation of Aboriginal and Torres Strait Islander health improvement initiatives.

#### Kimberley revalidation study

In addition to studying the implementation process, Kimberley Aboriginal and Torres Strait Islander women offered the KMMS as part of routine care will be invited to participate in the revalidation study. The revalidation will analyse the results of KMMS assessments, any further clinical assessments and support, and the routine care provided when screening for perinatal depression and/or anxiety (see below for detail). During this study, the only modification to the recommended standard of care in the Kimberley will be for a sample of women who score low risk on the KMMS to be offered a follow-up clinical assessment by a GP or mental health professional as part of revalidating the cut-point.

Women who do not consent to the study will continue with usual care and no identifying information will be collected on these women. De-identified information about the number, scores and basic demographics of all KMMS assessments will be requested from partner organisations as part of evaluating the implementation.

#### Pilbara and Far North Queensland validation study

In the Pilbara and FNQ selected health services have agreed to trial the KMMS instead of the EPDS to screen for perinatal depression and anxiety. Partner health services will ask perinatal women for consent to participate in the study. This includes completing the KMMS and providing feedback on the screening tool. All women scoring moderate or high on the KMMS and a sample of women scoring low on the KMMS will be referred for a further clinical assessment using the DMT. As in the Kimberley, the KMMS will be offered in accordance with the national EPDS screening schedule [4] and rescreening will involve completing a new Part 1 and continuing the yarn in the original Part 2.

Women who do not consent to the study can use the KMMS, but no identifying information will be collected on these women.

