### Sample size calculation

We plan to recruit an equal number of antenatal and postnatal women. The data from antenatal and postnatal women will be pooled for the main analysis, as there was no significant difference in KMMS or study GP assessments between antenatal and postnatal participants in the Kimberley validation study [13]. If there is no significant difference between the data from the three regions, these data will also be pooled.

For the validation/revalidation study, assuming there is a minimum sensitivity of 83% for screening for perinatal depression and anxiety and prevalence is at least 25% (based on the Kimberley validation study), using calculations by Buderer [32] a sample size of 868 paired KMMS and DMT assessments will detect a two-tailed 95% CI with a maximum width of ±5% (i.e., if sensitivity 83, 95% CI 78–88%). This is at the upper end of reported sensitivities for the EPDS compared to a reference standard assessment (59–100%) [33].

Based on the Kimberley validation study [13], we expect 65% of KMMS assessments to be referred for DMT and that at least 75% of the participants who are referred will have both the KMMS and DMT assessments completed (i.e., require 1780 KMMS to obtain 868 paired assessments). For the secondary analysis to determine changes in KMMS risk, we aim to assess as many participants as possible both antenatally and postnatally. As a conservative estimate, we will assume that at least 60% of participants will have KMMS administered at both time points. Recruiting 890 antenatal women (50% of the 1780 KMMS required) should provide at least 534 paired antenatal/postnatal KMMS assessments. In addition, approximately 356 women will be recruited postnatally to ensure that we have 890 antenatal and 890 postnatal KMMS assessments required for the main sample size calculation. Therefore, we initially aimed to recruit 1246 women (890 in the antenatal period and 356 women postnatally) to provide 868 paired KMMS / DMT assessments and 534 paired antenatal/postnatal KMMS assessments.

The complexity of establishing a partnership project across three remote regional areas has taken longer than anticipated; as such a revised sample size is 700 women across all three regions. Assuming 442 of the 700 women have paired KMMS and DMT assessments, this would allow us to detect a two-tailed 95% CI with a maximum width of ±7% (i.e., if sensitivity 83, 95% CI 76–90%).

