### Data analyses

#### Quantitative analysis

KMMS validation/revalidation internal consistency of Part 1 will be determined using Cronbach’s alpha [38]. Equivalence for identifying risk of depression and anxiety compared to the DMT will be determined from receiver operating characteristic curves. Sensitivity and specificity will be determined based on these cut-points.

Differences in characteristics between antenatal and postnatal participants, participants who are or are not diagnosed with depressive and/or anxiety disorders, and participants from different regions will be compared using χ^2^ tests for categorical data and Mann–Whitney tests for continuous non-parametric data. Change in KMMS risk (from low to moderate/high, or vice versa) will be compared using McNemar’s test. Descriptive statistical analysis will be used when assessing trends and patterns in user acceptability.

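### Reference assessment depends on the KMMS result, but the sample size treats the KMMS/DMT pairs as unselected and no verification-bias correction is named; unweighted analysis would overstate sensitivity by about 8 points on the plan's own inputs

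*Protocol article*

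**What the plan says.** Diagnostic accuracy of the KMMS against the DMT is the first primary outcome (Outcome measures).

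- **Who is referred.** For the new regions, the Pilbara and Far North Queensland validation study section says: "All women scoring moderate or high on the KMMS and a sample of women scoring low on the KMMS will be referred" for the DMT. The Kimberley revalidation study section provides for "a sample of women who score low risk on the KMMS to be offered a follow-up clinical assessment". Administering the KMMS sets the same pattern for all sites: every moderate or high result is referred, and only a proportion of low results. None of these sections gives the low-risk fraction or how those women are selected.
- **Analysis.** Quantitative analysis compares the KMMS with the DMT by ROC curves and continues: "Sensitivity and specificity will be determined based on these cut-points". It mentions neither weighting nor a correction for partial verification.
- **Sample size.** The calculation rests on "assuming there is a minimum sensitivity of 83% for screening for perinatal depression and anxiety and prevalence is at least 25" per cent, and states that "a sample size of 868 paired KMMS and DMT assessments will detect a two-tailed 95% CI with a maximum width of ±5" per cent. It then says "we expect 65% of KMMS assessments to be referred for DMT", with at least 75% of those referred completing both assessments, hence 1780 KMMS. The revised target is 700 women with 442 pairs for ±7%.
- **Source of the inputs.** Background reports the previous Kimberley validation as "sensitivity 83%; specificity 87%; positive predictive value 68" per cent.

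**The concern.** Whether a woman receives the reference standard depends on the result of the test under evaluation. Missed cases and true negatives both sit in the low-risk group, which is only sampled. In a plain two-by-two table of the pairs, false negatives are thinned out, so sensitivity comes out too high; true negatives are thinned out too, so specificity comes out too low. The ROC curve and any cut-point taken from it shift accordingly. Recruiting more women does not reduce this bias.

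The sample size section contains the conflict within itself. It sizes the pairs at 25% prevalence, which is right only for an unselected sample, and then gives a referral rate which, with its other inputs, shows that the pairs are enriched for moderate/high results.

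At stake is the decision on wider use of the KMMS. In the base case below, an unweighted analysis would report about 9% of affected women as missed when the true figure is 17%.

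**Working it through.** **Inputs.** Sensitivity (Se) 83%, prevalence (p) 25%, 65% referred, 75% completion, 868 pairs from 1780 KMMS, and 442 pairs from 700 women (Sample size calculation); specificity (Sp) 87% and PPV 68% (Background).

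**1. The plan's own figures reproduce.** Buderer: n = 1.96² × Se(1 − Se) / (W² × p).
- W = 0.05: 867.2, so 868.
- W = 0.07: 442.5, against 442 stated.
- 868 / (0.65 × 0.75) = 1780.5, against 1780 stated.
- PPV = 0.2075 / (0.2075 + 0.0975) = 68.0%, as reported, so 83/87/25 is a coherent set.

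The arithmetic is sound. The fault is in treating the pairs as unselected.

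**2. Implied low-risk referral fraction.** P(moderate/high) = 0.25 × 0.83 + 0.75 × 0.13 = 0.305. If all of these are referred and 65% are referred overall, the low-risk fraction is f = (0.65 − 0.305) / 0.695 = 0.496.

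**3. What unweighted pairs would show.** Completion cancels if it is equal in both risk groups.
- Se = 0.2075 / (0.2075 + 0.0425 × 0.496) = 90.8%, against 83% (+7.8 points).
- Sp = 0.6525 × 0.496 / (0.6525 × 0.496 + 0.0975) = 76.9%, against 87% (−10.1 points).
- Prevalence among pairs = (0.2075 + 0.0425 × 0.496) / 0.65 = 35.2%, not 25%.

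**4. Sensitivity to assumptions.**

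| Change from base case | Unweighted Se | Bias (points) |
|---|---|---|
| f = 0.75 | 86.7% | +3.7 |
| f = 0.30 | 94.2% | +11.2 |
| prevalence 15% (65% referred) | 90.0% | +7.0 |
| prevalence 35% (65% referred) | 91.7% | +8.7 |
| true Se 90% (65% referred) | 94.9% | +4.9 |
| true Se 95% (65% referred) | 97.6% | +2.6 |
| 442 of 700 paired, all moderate/high verified (f = 0.470) | 91.2% | +8.2 |

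**5. Precision of a weighted estimate.** With PPV a = 0.680, diseased share among low-risk b = 0.0425 / 0.695 = 0.0612, N screened, and n₊ and n₋ verified in the moderate/high and low groups:

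var(logit Se) = 1/(N × 0.305 × 0.695) + (1 − a)/(a × n₊) + (1 − b)/(b × n₋), and half-width = 1.96 × 0.83 × 0.17 × √var.

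- N = 1780, n₊ = 407, n₋ = 461 (868 pairs): ±5.3 points; simulation gives 5.3 to 5.4.
- N = 700, n₊ = 213.5, n₋ = 228.5 (442 pairs): ±7.6 points.
- N = 907 (442 / 0.4875), n₊ = 207, n₋ = 235: ±7.5 points.
- N = 1000 (700 women at the 1780:1246 ratio), n₊ = 229, n₋ = 213: ±7.8 points.

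The number of KMMS behind the 442 pairs is not stated, so the last three are alternatives. All are wider than the stated ±5% and ±7%.

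**The case against.** The strongest objection is that the article never says the analysis is unweighted. It is a condensed account, a statistical analysis plan may exist, and a verification-bias correction could sit there. That stands: a reader might infer that sensitivity *will* be overstated, but the text supports only that it would be if the pairs are analysed as they come. What survives is the sample size section, which positively applies population prevalence to selected pairs, so its stated precision is not that of a valid estimator whatever a later plan adds.

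Three further limits are fair.

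- A reader might infer that screeners hand-pick the low-risk women and that no later correction could repair this. No section says who chooses. Selection that depends on recorded variables could also be modelled.
- A reader might infer a firm bias of 8 to 10 points, always above the ±7% half-width. The upper end requires taking 83/87/25 as figures already distorted by partial verification, which the article does not say. The article also calls 83% a minimum and 25% a lower bound, and several rows of the table fall below 7 points.
- Moderate/high women are all referred, not all assessed: the DMT is used where possible, and 75% completion is expected. Lower completion among them would shrink the bias; higher completion would enlarge it.

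The design also looks repairable. Low-risk referral is deliberate, to check the cut-point, and Kimberley services will be asked for counts and scores of all KMMS assessments, so denominators for weighting appear obtainable there.

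**Conclusion.** The point holds in conditional form. Referral for the DMT depends on the KMMS result, the sample size treats the pairs as unselected, and no correction is named for the first primary outcome. Without weighting, the plan's own inputs give sensitivity of about 91% instead of 83%, specificity of about 77% instead of 87%, and pair prevalence of 35% instead of 25%. This rests on all moderate/high women being referred, equal completion by risk level, random low-risk selection and a low-risk fraction of about one half, which is derived and not stated. The direction of the bias is secure as long as low-risk women are verified less often than the others; its size is not. Separately, the stated ±5% and ±7% are slightly too narrow for an estimator that allows for the referral scheme.

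**What to change.** 1. **Quantitative analysis:** estimate sensitivity, specificity and the ROC curve with inverse-probability-of-verification (Begg-Greenes) weights. Build the weights from the KMMS category counts of all consented women screened, by region and KMMS category, with bootstrap intervals. Because the weights use completed DMTs, they also absorb completion that differs by risk level, provided completion is unrelated to disease within each category.
2. **Administering the KMMS, and the Kimberley and the Pilbara/Far North Queensland study sections:** state that the low-risk women referred for study purposes are drawn at random at a fixed, recorded fraction (about half, as the 65% implies), so that the weights are valid.
3. **Sample size calculation:** restate precision for the weighted estimator: about ±5.4 points for 868 pairs from 1780 KMMS, and about ±7.5 to ±7.8 points for 442 pairs assuming 700 to 1000 KMMS. State the number of KMMS assumed.

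The cost is analysis wording, a selection flag for low-risk women and slightly wider stated intervals. No extra women or assessments are needed. If the full analysis plan already specifies the weighting, item 1 reduces to a sentence in the protocol; items 2 and 3 remain unless it also covers the random selection and restated precision.
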